### Sample and Sampling—Complete

Using VHA data in its Corporate Data Warehouse obtained through its Veterans Affairs Informatics and Computing Infrastructure (VINCI), we identified an inception cohort (N=12,344) of veterans with SCI who received care in the VHA in FY 2009, but had no PrU in the 12 months prior to 2009 based on recorded ICD-9-CM codes. This group was considered free of PrUs for the purpose of the study. All structured hospital discharges (N=4090), outpatient encounters (N=5,202,804), and text data (N=9,888,245) for the cohort for FY 2009-2013 (October 1, 2008-September 30, 2013) were obtained through the VINCI. Veterans from this cohort were classified as having a PrU (ie, PrU+) or not having a PrU (ie, PrU-) during the study period based on both structured and text data. A total of 3860 PrUs were identified based on structured data and 829 based on text data alone, resulting in a total incidence of 4689 (4689/12,344, 37.99%) across the study period.

**Table 1 table1:** Risk factors categorized by structured, semistructured, and unstructured data sources.

Data source	Risk factor	Description or definition
Structured	Age	Age in years
	Gender	Male/female
	Race/ethnicity	Race/ethnicity
	Education level	Highest level of education
	VHA^a^ eligibility	VHA category, service connection
	Body weight	Body mass index, most recent weight, or change in weight
	Patient status	Inpatient/outpatient when pressure ulcer develops
	Pattern of preventive care	Consistency of annual well-patient exam
	Cognitive dysfunction	ICD-9-CM^b^ codes (ie, traumatic brain injury, dementia, and Alzheimer’s disease)
	Comorbidities—psychological	ICD-9-CM codes (ie, depression, anxiety, and posttraumatic stress disorder)
	Comorbidities—physical	ICD-9-CM codes (ie, diabetes mellitus, pulmonary disease, cardiac disease, renal disease, peripheral vascular disease, anemia, deep vein thrombosis, cancer, infection, lower extremity fractures, spasticity, autonomic dysreflexia, hypotension, and heterotopic ossification)
	Laboratory analysis	LOINC^c^ codes for lab values (ie, C-reactive protein, white blood cells, erythrocyte sedimentation rate, renal function, hemoglobin, hematocrit, albumin, and prealbumin)
	Medications	VHA formulary to identify chemotherapeutics, steroids, and benzodiazepines
	Surgery	ICD-9-CM codes of surgical procedures within previous 6 months of pressure ulcer development (administrative data)
	VHA-issued equipment	HCPCS^d^ codes for wheelchair cushion, bed support surface, and other equipment
	Telehealth	Distant observation of skin integrity
Semistructured	Motor/sensory assessment	American Spinal Cord Injury Association (ASIA) classification of SCI^e^ (eg, ASIA A= *Complete* injury of spinal cord)
	Level of injury	Cervical (C1-C8), thoracic (T1-T12), lumbar (L1-L5), and sacral (S1-S5)
	Alcohol use	Alcohol Use Disorders Identification Test—Consumption (AUDIT-C)
	Tobacco use	Current/former/nonsmoker
	Caregiver resources	Receiving aid and attendant, VHA-supported/reimbursed bowel/bladder care
	Duration of SCI	Years since injury/onset
	Sensation^f^	Ability to feel and relieve discomfort
	Moisture^f^	Exposure to moisture on trunk (ie, bowel/bladder leakage/accidents due to management or lack of containment, diarrhea, and diaphoresis)
	Mobility^f^	Ability to relieve pressure on high-risk areas (eg, trunk and heels)
	Activity^f^	Level of activity (ie, ability to get out of bed and ambulation)
	Nutrition^f^	Food intake malnutrition, undernutrition, and moderate/severe compromise
	Friction and shear^f^	Ability to minimize resistance between two parallel surfaces (ie, bed linens and skin)
	Living situation	Living arrangements (eg, alone, immediate family, extended family, roommate, and group setting)
Unstructured	Noncompliance with pressure redistribution	Patient refusal/decline to turn in bed
	Pain	Numeric pain rating scale (1-10) when pressure ulcer develops
	Pressure ulcer history	Previous pressure ulcer

^a^VHA: Veterans Health Administration.

^b^ICD-9-CM: International Classification of Diseases, Ninth Revision, Clinical Modification.

^c^LOINC: Logical Identifiers Names and Codes.

^d^HCPCS: Healthcare Common Procedural Coding System.

^e^SCI: spinal cord injury.

^f^Element of the Braden Scale.

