**Methods:**

This 5-year longitudinal, retrospective, cohort study targets 12,344 veterans with SCI who were cared for in the Veterans Health Administration (VHA) in fiscal year (FY) 2009 and had no record of a PrU in the prior 12 months. Potential risk factors identified in the literature were reviewed by an expert panel that prioritized factors and determined if these were found in structured data or unstructured form in narrative clinical notes for FY 2009-2013. These data are from the VHA enterprise Corporate Data Warehouse that is derived from the EHR structured (ie, coded in database/table) or narrative (ie, text in clinical notes) data for FY 2009-2013.

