### Data Extraction and Synthesis (Structured Data)—Ongoing

To determine whether the targeted structured variables were present in a patient’s record, we identified lists of codes (ie, ICD-9-CM codes) to operationally define the variables. When available, definitions employed by the VHA Support Service Center (VSSC), a centralized reporting portal, were used. The VSSC provides data summaries to VHA administrators and policy makers regarding business operations, clinical care, quality performance, and resource management. Otherwise, operational definitions were obtained from the AHRQ’s HCUP Clinical Classifications Software [20] or the Centers for Medicare and Medicaid Services definitions. Extraction routines were used to identify each occurrence of the variable in the patient’s record. These data were then transformed into single elements in the analytic data table based on clinically relevant temporal considerations. For example, some comorbidities such as diabetes were considered chronic conditions, while others such as fractures were framed in a 1-year period.

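### FY 2009 is both the entry year and an outcome year, so an ulcer already present at a veteran's first FY 2009 contact counts as incident

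*Protocol article*

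**What the plan says.** All references are to the protocol article.

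- **Entry** (Sample and Sampling). The inception cohort consists of those "who received care in the VHA in FY 2009, but had no PrU in the 12 months prior to 2009". The look-back rests on diagnosis codes alone. The Abstract words the same criterion as care "in fiscal year (FY) 2009 and had no record of a PrU in the prior 12 months".
- **Status at entry** (Sample and Sampling). "This group was considered free of PrUs for the purpose of the study". No check at the first FY 2009 contact is described.
- **Data window** (Sample and Sampling). Discharges, outpatient encounters and text "for the cohort for FY 2009-2013 (October 1, 2008-September 30, 2013) were obtained through the VINCI". The Abstract places the search for risk factors in the same years: the panel "determined if these were found in structured data or unstructured form in narrative clinical notes for FY 2009-2013".
- **Outcome count** (Sample and Sampling). PrU status is assigned over the study period from codes and text: 3860 from structured data plus 829 from text alone, 4689 of 12,344 (37.99%), reported as incidence.
- **Modelled outcome** (Variables Selection and Definition). It is a PrU documented within 1 year. The start of that year is not given.
- **Modelling sample** (Data Analysis). All 12,344 veterans are split 70/30 into derivation and validation samples.
- **Predictors that need history.** Table 1 lists change in weight and, for preventive care, "Consistency of annual well-patient exam". Data Extraction and Synthesis (Structured Data) adds that, unlike chronic conditions, "others such as fractures were framed in a 1-year period".

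**The concern.** The Objective is to estimate the probability of developing a PrU. That needs a point at which each veteran is known to be ulcer-free, predictors measured up to that point, and outcomes counted after it.

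Here, any VHA care in FY 2009 qualifies a veteran, and a PrU recorded in FY 2009 already counts. Suppose a veteran has no VHA record in the look-back and first attends during FY 2009 with an established ulcer. That veteran passes the screen, enters through that visit, and is scored as incident. Perfectly sensitive coding would not prevent it, because there is no earlier visit to code. A second route is open as well: the screen uses codes only while the outcome also uses text, so an ulcer noted only in text before entry can surface later as a new case.

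To that extent the model would learn the features of presenting with an ulcer rather than of developing one. Derivation and validation samples come from the same cohort, so internal validation would share the error and could not reveal it.

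**Working it through.** **1. The plan's own figure.** 3860 + 829 = 4689, and 4689/12,344 = 0.3799. The stated 37.99% reproduces. It covers the whole study period, FY 2009 included.

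**2. Does the 1-year outcome repair the overlap?** Take the two natural readings of its unstated start.
- The year starts at the beginning of FY 2009. Entry and outcome then coincide fully, and the problem falls entirely on the modelled outcome.
- The year starts after FY 2009. Veterans with a PrU in FY 2009 would have to leave the risk set, yet the analytic sample is still 12,344.

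Neither reading removes the problem as the plan stands.

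**3. Predictor history.** With extraction from 1 October 2008, an event *t* months into FY 2009 has *t* months of extracted data before it, fewer than 12. An event from FY 2010 onward has at least 12. The shortfall is confined to FY 2009 events and is worst for the earliest.

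**4. How many events might fall in FY 2009?** No yearly counts are given, so two assumptions are used.
- Equal spread: 4689/5 = 938, which is 938/12,344 = 7.60% of veterans and 20% of events.
- Constant hazard without deaths or losses: 1 - (1 - 0.3799)^(1/5) = 0.0911; 0.0911 × 12,344 = 1,125, which is 1,125/4,689 = 24% of events.

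These are all first events assumed for FY 2009, not ulcers already present at entry.

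**5. Sensitivity to an assumed prevalent share.** Let *E* be FY 2009 events and *p* the number already present at entry. Removing them gives a 1-year risk of (*E* - *p*)/(12,344 - *p*) and a 5-year figure of (4689 - *p*)/(12,344 - *p*). In each range the ends come from the two assumptions in step 4.

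| Assumed share | *p* | FY 2009 1-year risk | 5-year figure |
|---|---|---|---|
| 0% | 0 | 7.60-9.11% | 37.99% |
| 10% | 94-113 | 6.89-8.28% | 37.42-37.51% |
| 25% | 234-281 | 5.81-6.99% | 36.54-36.79% |
| 50% | 469-563 | 3.95-4.77% | 35.03-35.54% |

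The shares are illustrations; nothing in the article supports one over another. The pattern is what matters: the 5-year figure hardly moves, while the 1-year risk, which is the declared outcome, can move a good deal.

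**The case against.** The best case for the plan has four parts.

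- **Condensation.** This is an article, the structured-data work is still ongoing, and index dates and predictor windows usually sit in the full protocol or analysis plan. That stands for the detailed windows. It does not cover the entry rule, the incidence count or the modelling N: sampling is marked complete, and these are reported as fixed.
- **Start of follow-up.** No sentence says that everyone's follow-up begins on 1 October 2008. A reader might infer it, and might conclude that there is no baseline period at all. The article does not support that as a stated fact. A look-back for coded ulcers exists, and what is missing is an index date. The concern needs only that FY 2009 is used for both entry and outcome.
- **Predictors.** A reader might infer that history-dependent predictors can be filled only from the outcome period, or that they reflect care during or after the ulcer. Neither follows. Under the assumptions above, 76-80% of events fall in FY 2010-2013 and have at least a year of extracted data before them. Pre-study codes were evidently consulted for the look-back. The 1-year fracture window is not said to run past the event.
- **Few newcomers.** 5,202,804 outpatient encounters / 12,344 veterans / 5 years is about 84 per veteran-year, which suggests a heavily engaged cohort. This is a mean and says nothing about those with little contact, but it is a fair reason not to assume a large number.

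On wording, the look-back sentence omits FY before its second 2009. Read as calendar 2009, the look-back would overlap the first three months of the data window. The Abstract's wording and the FY 2009 earlier in the same sentence make a dropped FY more likely, so this is a query and not a defect to build on.

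**Conclusion.** The point holds in this form: FY 2009 serves both as entry year and as outcome time; ulcer-free status is presumed from codes, with no stated prior-contact requirement and no described check at first contact; and no veteran with an FY 2009 ulcer is removed before modelling. Followed as written, the plan scores an ulcer present at first FY 2009 contact as incident, and FY 2009 events lack a full year of prior predictor data.

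The size cannot be derived. It would be wrong to read 1,125, or 24%, as the number misclassified: that is an assumed total of FY 2009 events, with 938 (20%) under the other assumption, and the prevalent part of it is unknown. Any effect falls mainly on the 1-year risk and only slightly on the 5-year 37.99%. Because the analysis is still planned, this is a cheap improvement to make now.

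**What to change.** Use FY 2009 as the baseline year:

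1. Measure predictors, and confirm absence of PrU by both codes and text, from 1 October 2008 to 30 September 2009.
2. Start the 1-year outcome window on 1 October 2009.
3. Restate N and incidence for the resulting cohort.
4. State that 2009 in the look-back means FY 2009, if that is intended.

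No new extraction is needed. The entry criterion already guarantees VHA contact in the baseline year.

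**Cost.** FY 2009 events are lost as outcomes, about 20-24% of the total under the assumptions above. Removing those veterans leaves 12,344 - 1,125 = 11,219 to 12,344 - 938 = 11,406, with 4,689 - 1,125 = 3,564 to 4,689 - 938 = 3,751 first events over FY 2010-2013 (31.8-32.9%). A 1-year window uses only the FY 2010 part of these. Deaths in FY 2009 are not counted here and would lower N further. The cohort becomes veterans alive and ulcer-free at the end of FY 2009, and the report should say that the model applies to them.

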### Variables Selection and Definition—Ongoing

The dependent variable for this study will be documentation of the occurrence of a PrU in the EHR within 1 year (ie, 1-year incidence risk of PrU). The definition of the presence of a PrU used for case identification is based on ICD-9-CM codes (707.0-707.9) and the application of the classification algorithm based on text analysis or a combination of these two sources, depending on what is found to be more accurate. The potential independent variables for this study include the risk factors that were identified through a literature review and validated by expert panel discussion. The final list of potential risk factors, with input from the expert panel, will be extracted from multiple tables in the EHR, or from semistructured and unstructured text notes, for use in analysis. Three sets of candidate predictors based on data sources will be generated to develop each risk model: (1) structured data extracted directly from the EHR, (2) Braden scores, and (3) a combination of existing structured data and data extracted from text through the NLP processes.

The investigators conducted a comprehensive literature review generating a list of approximately 50 potential independent variables or risk factors (eg, demographics, diseases status, comorbidities, health behaviors, psychosocial factors, and home care). This list was reviewed by the expert panel for logical consistency, completeness, clinical relevance, and whether they were modifiable or not. The panel identified high-priority risk factors and discussed practical considerations including where the risk factor might be located in the EHR, how reliable these data might be, and alternative ways to document risk factors. Subsequently, persistent moisture on the skin, the type of living situation of the patient, evidence of malnutrition, and documentation that the patient took steps to redistribute their weight during the day were targeted as risk factors available in unstructured data. Structured data contained elements of the Braden Scale, lab values, and other variables (see Table 1). Several coding systems are used to classify structured data variables, including the ICD-9-CM, Logical Identifiers Names and Codes (LOINC), and the Healthcare Common Procedural Coding System (HCPCS). International Classification of Diseases, Tenth Revision, Clinical Modification (ICD-10-CM) codes were not implemented in the VHA until after the end of this study and are not used.

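### Three candidate predictors (patient status, surgery, pain) are defined relative to the pressure ulcer itself, so they have no defined value for ulcer-free veterans or at the time a 1-year risk is scored

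*Protocol article*

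**What the plan says.** Table 1 of the protocol article (under Sample and Sampling) ties three risk factors to the occurrence of the ulcer:

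- Patient status (structured): "Inpatient/outpatient when pressure ulcer develops".
- Surgery (structured): "surgical procedures within previous 6 months of pressure ulcer development".
- Pain (unstructured): "Numeric pain rating scale (1-10) when pressure ulcer develops".

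These are candidate predictors. Variables Selection and Definition states that "Three sets of candidate predictors based on data sources will be generated to develop each risk model": structured data, Braden scores, and structured data combined with data extracted from text. Patient status and surgery therefore enter both the structured and the combined set. Pain, listed as text-derived, enters only the combined set. The same section sets the outcome as a PrU documented within 1 year.

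Sample and Sampling says that veterans were "classified as having a PrU (ie, PrU+) or not having a PrU (ie, PrU-) during the study period". Model Development fits both groups together by logistic regression, with automated selection on information criteria.

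The only timing rule for building predictors is in Data Extraction and Synthesis (Structured Data): "These data were then transformed into single elements in the analytic data table based on clinically relevant temporal considerations". Its examples are diabetes as a chronic condition and fractures framed in a 1-year period. The article gives no reference date for veterans without an ulcer.

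**The concern.** A predictor in a risk model must be measurable in the same way in people who will and will not have the event, at a time before the outcome is known. These three are fixed by the date of the event. Veterans without an ulcer have no such date, so their values are undefined or must come from some other rule. Any rule that differs between the groups builds outcome status into the predictor.

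The definitions also conflict with the aim. The Objective in the Abstract is to estimate the probability of developing a PrU. At that moment there is no ulcer, and so no setting, pain score or surgical look-back at its onset.

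The main comparisons are at stake. Hypotheses 1 and 2 set the new models against a Braden model that contains none of the three variables, so discrimination created by the anchoring would count only for the new models. Selection on information criteria would tend to keep such variables, and the ranking by Z-score could put them high on the lists given to clinicians. The random 70/30 split applies the same definitions to both parts, so validation AUC and calibration would not show the fault.

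**Working it through.** **1. The article's own figures.** 3860 PrUs from structured data + 829 from text alone = 4689; 4689/12,344 = 37.99%, as stated. Taking this as a count of veterans, as the article does, 12,344 − 4689 = 7655 (62.0%) have no ulcer date at any time in the 5 years. The split also reproduces: 0.70 × 12,344 = 8640.8 and 0.30 × 12,344 = 3703.2, against 8641 and 3703.

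**2. Surgery with no true effect.** Assume the same Poisson rate *r* of operations per year in both groups. The article gives no rate, so a range of 0.05 to 0.4 is used. Then P(any operation in *t* years) = 1 − exp(−*rt*), and the odds are exp(*rt*) − 1. Cases are read over 6 months (*t* = 0.5), as Table 1 says. The window for non-cases is not stated, so two are tried: 1 year, which matches the outcome horizon and the fracture example, and 5 years, the whole extract. The spurious odds ratio is [exp(0.5*r*) − 1] / [exp(*rt*) − 1].

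| *r* per year | P, 6 months | P, 1 year | P, 5 years | OR, non-cases over 1 year | OR, non-cases over 5 years |
|---|---|---|---|---|---|
| 0.05 | 0.025 | 0.049 | 0.221 | 0.494 | 0.089 |
| 0.1 | 0.049 | 0.095 | 0.393 | 0.488 | 0.079 |
| 0.2 | 0.095 | 0.181 | 0.632 | 0.475 | 0.061 |
| 0.4 | 0.181 | 0.330 | 0.865 | 0.450 | 0.035 |

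With 6 months in both groups, numerator and denominator are equal and the odds ratio is 1.

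**3. The same on the AUC scale.** For a binary predictor, AUC = 0.5 + [P(x=1 | PrU+) − P(x=1 | PrU−)] / 2. With non-cases read over 1 year, *r* = 0.4 gives 0.5 + (0.181 − 0.330)/2 = 0.426, or 0.574 once the model fits the negative sign. If non-cases are coded as having had no surgery, *r* = 0.1, 0.2 and 0.4 give 0.524, 0.548 and 0.591. With equal windows the AUC is 0.50.

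**4. Patient status with no true effect.** Suppose ulcer-free veterans are coded as outpatients by default and a share *q* of cases were inpatients at onset (assumed). Then AUC = 0.5 + *q*/2: 0.55 for *q* = 0.10, 0.65 for *q* = 0.30 and 0.75 for *q* = 0.50. Every veteran coded as an inpatient would be a case.

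**5. Which hypotheses are exposed.**

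| Variable | Braden model | Structured model | Combined model |
|---|---|---|---|
| Patient status | no | yes | yes |
| Surgery | no | yes | yes |
| Pain | no | no | yes |

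Hypotheses 1 and 2 compare a model that has anchored variables with one that has none. In Hypothesis 3 two of the three variables are shared. Leakage through those could mask a real gain from text data, whereas leakage through pain could create one.

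**The case against.** The strongest defence is that the article condenses a fuller document. Variable definition and structured extraction are marked ongoing, operational definitions of codes are still being created, and analysis is only planned. An unreported pseudo-index date for ulcer-free veterans could remove much of the leakage. Table 1 also lists candidates only, and Model Development favours variables that are easy to assess in practice, so the three may not reach the final model.

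This stands as far as the size of the bias goes: it is conditional on coding that is not reported. It does not rescue the definitions. They are stated, not omitted, and even with a pseudo-index date a value recorded when the ulcer develops is unavailable when risk is scored.

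Stronger readings that a reader might infer are not supported:

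- *Near-perfect discrimination.* An AUC of 1.0 arises only if missingness itself enters the model, which the article does not propose. A complete-case fit would drop every ulcer-free veteran and fail visibly.
- *A 5-year window for non-cases.* This appears nowhere; it is the extreme of the range above.
- *All three hypotheses biased towards the new models.* The direction for Hypothesis 3 is not established.
- *A Braden model free of leakage.* It lacks the three anchored variables, but the timing of Braden scores is equally unstated.
- *Leakage through equipment, telehealth, refusal to turn or ulcer history.* Table 1 gives these no wrong timing; the article merely states no cut-off. The annotation schema in Table 3 does record temporality and whether an ulcer mention is historical.
- *A final tool that cannot be scored.* That follows only if the three variables survive selection.

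**Conclusion.** The point holds for three stated definitions: patient status, surgery and pain. Each is anchored to an event that 62% of the cohort did not have over 5 years and that nobody has had when a 1-year risk is estimated. As written, none can be a valid prospective predictor, and this does not depend on any assumed rate.

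The size of the bias does depend on assumptions. For surgery with no true effect and 0.05 to 0.4 operations per year, the spurious odds ratio is about 0.49 to 0.45 against a 1-year window, 0.09 to 0.03 against a 5-year window, and 1 with equal windows. Hypotheses 1 and 2 can be biased; for Hypothesis 3 the direction is uncertain. The planned internal validation cannot detect the problem. It should be corrected before the analytic dataset is built.

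**What to change.** - Set one prediction (index) date that does not depend on the outcome. Restrict the cohort to veterans with no PrU before it, and count the 1-year outcome from it.
- Redefine the three variables as inpatient or outpatient at index, surgery in the 6 months before index, and last pain score before index, with the same look-back for PrU+ and PrU− veterans.
- Apply the same pre-index cut-off to every other predictor, including Braden scores and PrU history.
- Do not instead discard values dated on or after the first evidence of an ulcer: that makes the window length depend on the outcome again.

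October 1, 2009 is one workable index date, because the extract starts on October 1, 2008 and FY 2009 then supplies the look-back. Veterans with a first PrU during FY 2009 must then be excluded, since the cohort was screened only for the 12 months before 2009.

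**Cost.** The work is new definitions and date filters on data already extracted. Some early events and veterans are lost; the article does not give the number. AUCs may look less favourable.
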